### Parent-reported secondary outcomes

The following parent-reported outcome measures will be completed by the child’s parent/guardian or caregiver(s) and assisted by the assessor at each timepoint:

***The Child Health Utility-9 Dimensions*****(CHU9D)** provides a preference-based utility index for assessing health-related QoL (HRQL) in children where the nine dimensions reflect paediatric perspectives of HRQL.^124^ The parent proxy version will be used, completed by the parent or guardian to provide a utility index for economic evaluations.^125^ The CHU9D has demonstrated moderate test–retest reliability (ICC 0.52 and 0.60).^126^

***The Caregiver Priorities andChildHealth Index of Life with Disabilities (CPCHILD)*****^127^**questionnaire assesses HRQoL across six domains: Personal Care and Activities of Daily Living; Positioning, Transferring and Mobility; Comfort/Emotions; Communication & Social Interaction; Health and Overall QOL. The CPCHILD has demonstrated content validity, reliability and construct validity for ease of caregiving, functional limitations, comfort, health and well-being of children with severe CP, test–retest reliability (ICC 0.97 and 0.88–0.96 for domain scores) and internal consistency (Cronbach’s alpha>0.70).^127^

***The Pediatric Evaluation of Disability Inventory Computer Adaptive Test (PEDI-CAT)*** is a valid and reliable parent-reported assessment of a child’s function in four domains^128^: Daily activities; Mobility; Social/Cognitive and Responsibility, using scaled scores (Rasch) that have good validity and reliability.^129^ Scaled scores (possible range 20–80) for each domain provide more precise results in the extreme ranges, compared with normative standard scores, and are recommended to track function progress in children with substantial delays.^129^

***Health Resource Use (HRU)*** questionnaire^130^ will be completed by the parent or guardian and supplemented by Medicare Benefits Schedule (MBS) and Pharmaceutical Benefits Scheme (PBS) data. The HRU includes data on screening, therapy frequency and duration, hospital admissions, medical visits, operations, medication, equipment and parent time for appointments. Standard cost sources (MBS, PBS, hospital, diagnosis-related groups for inpatient and outpatient services) will be applied to resource use and total cost of care calculated per child aged 2–12 years. The cost–consequence analysis will report health outcomes to demonstrate value for money, including best possible musculoskeletal health, physical function, greater QoL, non-health effects and non-patient effects (carer well-being and QoL).

### Sample size and power calculations

The total number of participants with data in line with the primary study objectives is expected to be n=450. This assumes 4 years of data from 90% of 500 enrolled participants and is based on attrition rates in previous National Health and Medical Research Council (NHMRC) funded cohorts run by the CI team. If the HD prevalence in approximately 70% of the total cohort is assumed, the AusCP MSK study will have 90% statistical power (α=0.05) to detect absolute differences between binary risk factor categories exceeding 12%. This corresponds to detecting relative risks (RRs) falling below 0.80 or surpassing 1.24. Even when risk factors are unbalanced in a 4:1 ratio, we will be able to identify RRs of <0.74 or >1.35. For scoliosis incidence, if an overall cumulative incidence of 25% is assumed, the study will be able to detect absolute between-group differences of >11%. Note that this is an underestimate of power due to the repeated annual measurements for each child.

The bone quality cohort (C) will recruit 30 children with CP, detecting between-group differences >1.25 SD with 90% power, which are smaller differences than observed when comparing children with mild Osteogenesis Imperfecta compared with TDC.^131^

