## Methods and analysis

### Aims and hypotheses

The AusCP MSK primary study objective is to:

Identify early biomarkers of onset/progression of musculoskeletal complications (hip displacement, scoliosis, fragility fracture) that predict the severity and rate of progression of musculoskeletal complications (MP>30%, Cobb angle>10°, lateral distal femur (LDF) bone mineral density (BMD) Z-score< −2.0) at 8–13 years, leading to natural history data that can be used to inform early intervention clinical trials and identify new therapeutic targets.

The AusCP MSK secondary study objectives are to:

Identify the relationship between early brain structure (clinical MRIs), aetiology of CP and musculoskeletal development at 1–4 years of age on disability outcomes at 8–13 years of age.Determine the costs and consequences of medical and allied health resource use (HRU), and poor QoL at 8–13 years of age, related to severity of musculoskeletal complications at 4–9 years of age.Determine prevalence, HRU costs and clinical characteristics of children and adolescents with CP who sustain a pathological fracture, evaluate complementary data for CP patient bone quality and develop a predictive model for fracture.

These aims will be explored through the following hypotheses:

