Higher prevalence of musculoskeletal risk factors for hip displacement, scoliosis, reduced BMD for age, such as Gross Motor Function Measure (GMFM), HPA/sedentary behaviour, nutritional status, body composition (fat mass/fat free mass on DXA), at 4–9 years of age will lead to poorer musculoskeletal outcomes at 8–13 years of age.The location and extent of the brain lesion(s) on structural MRI, pathophysiology of CP (motor type and distribution), motor capacity (GMFM-88) at 4–9 years of age will predict severity of musculoskeletal complications (hip displacement, scoliosis, bone fragility) and performance outcomes (Pediatric Evaluation of Disability Inventory, Computer Adapted Test, PEDI-CAT) at 8–13 years of age.The location, extent of the brain lesion(s) on semiquantitative MRI (<6 years) will predict the severity of musculoskeletal outcomes (MP>30%, Cobb>10°), at 8–13 years of age.Healthcare costs will be higher for children with greater adverse musculoskeletal biomarkers at 4–9 years of age and will lead to poorer outcomes and QoL (consequences) at 8–13 years of age.Pathologic fracture will be a major health burden in children with CP that increases with GMFCS and age.The identification of children with CP at greatest risk of fracture through a predictive tool will enable the determination of prognosis, inform therapeutic action and reduce fracture burden.Bone quality of children with moderate-to-severe CP will be abnormal compared with TDC;Genetic variation will influence onset and progression of musculoskeletal complications in CP.

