**Figure 2 F2:**
[figure not shown]
Directed acyclic graph model of musculoskeletal complications in children with cerebral palsy. GMFM, Gross Motor Function Measure; HPA, habitual physical activity; MP, migration percentage; PEDI-CAT, Pediatric Evaluation of Disability Inventory, Computer Adapted Test; SB, sedentary behaviour.

When constructing predictive models, important variables will be examined individually first before a final multivariable model is selected using Bayesian information criteria. Model calibration will be tested graphically, and internal calibration will use bootstrap resampling. Missing data will be treated as case-by-case basis depending on the observed pattern of missingness. For example, if data are ‘missing at random’, we will use multiple imputation methods and if data are ‘not missing at random’, we will use a pattern-mixture model. Adjustments for multiple comparisons will be made for each separate suite of analyses as appropriate, bearing in mind the type I and type II error rates for each suite.

In addition to the primary statistical analysis, a cost–consequence analysis will be performed to attain a better understanding of the value and costs of a national approach to better decision-making regarding hip, spine and bone fragility complications in CP. The cost–consequence analysis will capture the direct costs of medical care and direct non-medical costs from the HRU parent-reported questionnaire. The cost-consequence analysis will report costs and outcomes in a simple and disaggregated format to help policymakers better understand the effects of prevention programmes for musculoskeletal problems across costs and outcomes. The analysis will be performed in a 4-year time horizon with a 3% discount rate to account for time preference.

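### The 90% power figures are for a single unadjusted test at α=0.05, so they do not apply to any test that the plan adjusts for multiple comparisons

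*Protocol article*

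**What the plan says.** **Sample size and power calculations.** The analysable number is given as: "The total number of participants with data in line with the primary study objectives is expected to be n=450". Its basis is: "This assumes 4 years of data from 90% of 500 enrolled participants". For hip displacement the section continues: "If the HD prevalence in approximately 70% of the total cohort is assumed", then "the AusCP MSK study will have 90% statistical power (α=0.05) to detect absolute differences between binary risk factor categories exceeding 12" percentage points, and adds: "This corresponds to detecting relative risks (RRs) falling below 0.80 or surpassing 1.24". For scoliosis it assumes 25% overall cumulative incidence and claims detection of differences above 11 points. It closes by saying that power is understated because each child is measured every year. It makes no allowance for multiple testing.

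**Statistical analysis (text after the Figure 2 caption).** "Adjustments for multiple comparisons will be made for each separate suite of analyses as appropriate". The sentence goes on to say that type I and type II error rates will be kept in mind for each suite. It does not say what a suite contains, how many tests it holds or which method will be used.

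**Aims and hypotheses.** The primary objective seeks early biomarkers "that predict the severity and rate of progression of musculoskeletal complications" and lists three of these: hip displacement, scoliosis and low distal femoral bone density. The first hypothesis gives examples of risk factors: "Gross Motor Function Measure (GMFM), HPA/sedentary behaviour, nutritional status, body composition (fat mass/fat free mass on DXA".

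**The concern.** The article makes two statements that do not fit together. One gives power for a test at α=0.05. The other commits to adjusting for multiple comparisons, as appropriate, within suites of analyses. A test adjusted with others in its suite has a stricter threshold and so less power at the same difference.

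The primary objective is to find early biomarkers. A reader who takes 90% power at face value may read a null result as fairly strong evidence against a difference of about 12 points (hip) or 11 points (scoliosis). If the test was adjusted, the chance of missing such a difference is well above the 10% implied, and a real biomarker could be set aside.

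**Working it through.** **Inputs.** From the sample size section: 450 analysable children; overall rates of 70% (hip) and 25% (scoliosis); printed differences of 12 and 11 points; α=0.05; power 90%. Assumed, because the article does not say: a two-sided test, a 1:1 split (225 per group), groups centred on the overall rate, and Bonferroni (α=0.05/m) as the reference adjustment. The number of tests adjusted together, m, is not stated, so a range is shown.

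**Formula.** With difference d, overall rate p̄ and group rates p₁, p₂ = p̄ ± d/2:

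- SE₀ = √[2p̄(1−p̄)/225]
- SE₁ = √{[p₁(1−p₁)+p₂(1−p₂)]/225}
- power = Φ[(d − z·SE₀)/SE₁], where z is the two-sided critical value

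**Step 1: the plan's own figures, without adjustment (z=1.960).**

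- Hip, 76% v 64%: SE₀ = √(0.42/225) = 0.04320; SE₁ = √(0.4128/225) = 0.04283. Power = Φ[(0.12 − 0.0847)/0.04283] = Φ(0.825) = 79.5%.
- Scoliosis, 30.5% v 19.5%: SE₀ = √(0.375/225) = 0.04082; SE₁ = √(0.36895/225) = 0.04049. Power = Φ[(0.11 − 0.0800)/0.04049] = Φ(0.741) = 77.0%.

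The printed 90% is not reproduced. The 12 and 11 points sit close to the differences with 80% power (12.1 and 11.4 points). Solving for 90% power at α=0.05 gives 13.9 points for hip and 13.2 for scoliosis. Other variance formulas do not close the gap for hip (80.0% unpooled, 79.7% arcsine).

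**Step 2: the effect of adjustment alone.** Start from the differences that do have 90% power at α=0.05, so that the Step 1 error plays no part. For hip with m=3, z=2.394: (0.1394 − 2.394 × 0.04320)/0.04270 = 0.842, and Φ(0.842) = 80%.

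| m | α per test | Power at 13.9 (hip) or 13.2 (scoliosis) points | Hip difference with 90% power | Scoliosis difference with 90% power |
|---|---|---|---|---|
| 1 | 0.05 | 90% | 13.9 | 13.2 |
| 2 | 0.025 | 84% | 15.1 | 14.3 |
| 3 | 0.0167 | 80% | 15.8 | 14.9 |
| 4 | 0.0125 | 77% | 16.2 | 15.3 |
| 12 | 0.0042 | 64% | 17.8 | 16.8 |

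**Step 3: both causes together, at the printed differences.**

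| m | Hip, 12 points | Scoliosis, 11 points |
|---|---|---|
| 1 | 79.5% | 77.0% |
| 2 | 70.6% | 67.6% |
| 3 | 65.1% | 61.9% |
| 4 | 61.1% | 57.9% |
| 12 | 46.5% | 43.2% |

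For hip with m=3, the total shortfall from 90% is 90 − 65.1 = 24.9 points. Of this, 90 − 79.5 = 10.5 points exist before any adjustment and 79.5 − 65.1 = 14.4 points come from the adjustment.

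**The case against.** **The text does not fix a family.** Adjustment is per suite and as appropriate, with type II error to be considered. A suite might be one complication, one aim or one model, and some suites might not be adjusted at all. This stands. A reader might infer that adjustment spans all the risk factors and all three complications, giving m=12 or more. The article does not say so: the risk factors are introduced as examples, and no family is defined. The row for m=12 only illustrates the upper part of the range.

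**Family make-up and method belong in a SAP.** This also stands, and their absence is not the point. The article itself prints both the power claim and the commitment to adjust, and the claim does not say that it is limited to unadjusted tests.

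**The section discloses α=0.05 and never claims power after adjustment.** True, and this makes it a matter of restating scope. But nothing warns the reader that the figure stops applying once a test is adjusted.

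**At the printed relative risks, power is higher.** With 70% overall, RR 0.80 is 15.6 points and RR 1.24 is 15.0 points. Power there is 95.2% and 93.7% unadjusted, 91.6% and 89.4% with m=2, and 89.0% and 86.3% with m=3. This is correct, but those ratios do not match the 12 points they are said to correspond to: 64/76 = 0.84 and 76/64 = 1.19. They therefore cannot support the 12-point claim.

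**Repeated annual measurements add power.** The article says so without a figure. The gain cannot be checked from the document, so it cannot be set against a loss that can be calculated.

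**The planned analyses are mixed-effects models and BIC selection, not two-proportion tests.** True. The two-proportion calculation is used because the sample size section frames its claim as differences between two risk-factor categories.

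**Conclusion.** The point holds in a limited form. The 90% power figures belong to a single unadjusted test at α=0.05 and do not apply to any test adjusted under the Statistical analysis section. The direction does not depend on the family size, because even two adjusted tests take 90% down to 84%. The size does depend on it: 80% for three, 77% for four, 64% for twelve. Those values rest on a two-sided test, a 1:1 split, 450 children and Bonferroni.

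A reader might infer that multiplicity alone takes the study from 90% to 65% (hip) and 62% (scoliosis) with three tests. The document does not support that. At the printed 12 and 11 points, power is already about 79.5% and 77.0% with no adjustment, so the lower figures combine two separate causes.

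**What to change.** In Sample size and power calculations:

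1. Restate the differences detectable with 90% power, for one unadjusted two-sided test at α=0.05 with 450 children split 1:1, as about 14 points for hip displacement and about 13 points for scoliosis.
2. Say that the 90% claim is limited to such tests.
3. For any suite that will be adjusted, give the detectable differences at the α it leaves. If three tests are adjusted together (α=0.0167), for example, these are about 16 points for hip and 15 points for scoliosis.

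The cost is a change of wording. The stated detectable differences become less favourable, and no extra participants are needed.

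### The 12-point (hip) and 11-point (scoliosis) detectable differences match about 80% and 77% power, not 90%, and 12 points does not correspond to the relative risks printed with it

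*Protocol article*

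**What the plan says.** All the figures stand in the protocol article, section Sample size and power calculations.

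- **Number with data:** "The total number of participants with data in line with the primary study objectives is expected to be n=450". The basis is given as "This assumes 4 years of data from 90% of 500 enrolled participants", that is 500 × 0.90 = 450.
- **Hip displacement:** the condition is "If the HD prevalence in approximately 70% of the total cohort is assumed". The claim is that "the AusCP MSK study will have 90% statistical power (α=0.05) to detect absolute differences between binary risk factor categories exceeding 12" (percentage points).
- **Relative risks:** the next sentence reads "This corresponds to detecting relative risks (RRs) falling below 0.80 or surpassing 1.24". For risk factors split 4:1, the article gives relative risks below 0.74 or above 1.35.
- **Scoliosis:** with 25% cumulative incidence overall, "the study will be able to detect absolute between-group differences of >11" (percentage points). Power is not restated here, so the 90% of the hip sentence carries over.
- **Closing remark:** "Note that this is an underestimate of power due to the repeated annual measurements for each child".

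**The concern.** The article gives every input needed to recompute its detectable differences, and the recomputed values differ. Both absolute differences sit close to the values for 80% power. There is also a conflict that does not depend on the choice of test: a 12-point gap around 70% cannot be a relative risk of 0.80 or 1.24, so at least one of two adjacent sentences is wrong.

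These figures are the quantitative support for the primary objective, which is to identify early biomarkers of hip displacement, scoliosis and bone fragility. If a risk factor truly shifts risk by 12 points (hip) or 11 points (scoliosis), it would be missed about 20% or 23% of the time, rather than the 10% that the text implies. A reader who relies on the printed figures would take a null result as stronger evidence than it is.

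**Working it through.** **Inputs from the article.** N = 450; α = 0.05; power 90%; overall risk 70% (hip) and 25% (scoliosis).

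**Inputs inferred.**
- Balanced categories, 225 v 225, because the 4:1 case is introduced afterwards as the unfavourable variant.
- A two-sided test, because relative risks are given in both directions. The article does not state sidedness.
- Group risks placed symmetrically around the overall risk, because both rates are described as those of the whole cohort.

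**Formula** (two-proportion z-test, m per group, mean risk p, difference d):
- SE0 = √(2p(1−p)/m) and SE1 = √((p1(1−p1) + p2(1−p2))/m)
- power = Φ((d − 1.96·SE0)/SE1)

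**Power at the printed differences**
- Hip, 76% v 64%: SE0 = √(0.42/225) = 0.0432; SE1 = √(0.4128/225) = 0.0428; z = (0.12 − 0.0847)/0.0428 = 0.82; power **79.5%**.
- Scoliosis, 30.5% v 19.5%: SE0 = √(0.375/225) = 0.0408; SE1 = √(0.36895/225) = 0.0405; z = (0.11 − 0.0800)/0.0405 = 0.74; power **77.0%**.

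The stated 90% is not reproduced. Other forms of the test agree: unpooled variance gives 80.0% and 77.5%, arcsine 79.7% and 77.3%, and continuity correction 76.4% and 73.6%.

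**Detectable difference**, solving d = 1.96·SE0 + z·SE1, with z = 1.2816 for 90% power and 0.8416 for 80%:

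| Outcome | Printed | 80% power | 90% power |
|---|---|---|---|
| Hip (70% overall) | 12 | 12.1 | 13.9 (77.0% v 63.0%; RR 1.22 or 0.82) |
| Scoliosis (25% overall) | 11 | 11.4 | 13.2 |

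Keeping 12 and 11 points at 90% power would take about 610 and 648 children with data. Even all 500 enrolled would give only 13.2 and 12.5 points.

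**Absolute against relative scale, hip**
- 12 points around 70%: 0.76/0.64 = 1.19; inverse 0.84.
- RR 1.24 around 70%: lower risk = 1.40/2.24 = 62.5%, higher = 77.5%; gap 15.0 points, power 93.7%.
- RR 0.80 around 70%: higher risk = 1.40/1.80 = 77.8%, lower = 62.2%; gap 15.6 points, power 95.2%.
- If 70% is instead the reference-group risk: RR 0.80 is 14 points (0.70 × 0.20) and RR 1.24 is 16.8 points (0.70 × 0.24).
- A 12-point gap gives RR 0.80 only from a reference risk of 60% (0.12/0.20), and RR 1.24 only from 50% (0.12/0.24).

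**4:1 split (360 v 90), hip.** With the smaller group at lower risk, 90% power is reached at 55.7% v 73.6%, a gap of 17.9 points and RR 0.76 or, inverted, 1.32. The printed 0.74 and 1.35 (1/0.74 = 1.35) have about 93% power in that configuration.

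**The case against.** **Another reading of the inputs might give 90%.**
- A one-sided test with 450 children gives 87.3% (hip) and 85.5% (scoliosis).
- A one-sided test on all 500 enrolled gives 90.2% and 88.6%, but this contradicts the stated 450.
- A one-sided test with the reference group fixed at the stated rate, in the favourable direction only, gives 91.1% and 90.5%. This contradicts rates described as those of the whole cohort.
- A two-sided test with the reference group fixed gives 84.9% or 75.7% (hip) and 71.9% or 84.0% (scoliosis), depending on direction.

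The one-sided readings also clash with relative risks given in both directions, and none of these readings makes 12 points equal RR 0.80 or 1.24.

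**Repeated measurements add power.** This partly stands. The section Statistical analysis plans mixed-effects logistic models for binary outcomes, so status at several visits can contribute. The gain depends on the within-child correlation (ICC), which the article does not give. Assuming four measurements and a design effect of 1 + 3·ICC, power for 12 points would be 94% at an ICC of 0.5, 89% at 0.7 and 83% at 0.9. But the article presents this gain as additional to its 90%, so it cannot be the source of the 90%. A reader might infer that the remark is wrong and should go; the documents do not support that.

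**The printed relative risks are sound.** This stands. A reader might infer that the design lacks 90% power altogether, or that the 4:1 relative risks are wrong too. Neither follows. At 90% power the balanced pair is 0.82 and 1.22, so the printed 0.80 and 1.24 are slightly conservative. The printed 4:1 pair is likewise close to, and slightly more conservative than, 0.76 and 1.32.

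**Multiplicity.** A reader might also infer that power at α = 0.05 conflicts with the planned adjustment for multiple comparisons. The article leaves that adjustment to each suite of analyses and fixes no number of tests, so there is no contradiction to report.

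**Conclusion.** The point holds for the two absolute differences and for the sentence that equates 12 points with the relative risks. The differences are too favourable by about 2 percentage points each: 12 should be about 14, and 11 about 13. The conflict between 12 points and RR 0.80 or 1.24 concerns hip displacement only, because no relative risk is printed for scoliosis.

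The size rests on 225 v 225, a two-sided test and risks placed around the stated overall rates. The 90% for scoliosis is implied rather than stated. The enrolment target is unaffected: 450 follows from 500 and 90% retention and was not derived from the 12 points.

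**What to change.** Replace the absolute differences with either:

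- 90% power for differences of about 14 points in hip displacement (relative risk below 0.82 or above 1.22) and about 13 points in scoliosis; or
- roughly 80% power for 12 points in hip displacement and 77% for 11 points in scoliosis.

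Under either wording, make the absolute difference and the relative risks beside it describe the same effect; for the second, 12 points is a relative risk of 0.84 or 1.19. State the power for scoliosis explicitly, and say that the test is two-sided. Leave the 4:1 relative risks as printed. The repeated-measures remark can stay, provided it is not used to support the 90%.

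The cost is wording only: no extra participants and no change to the analysis.

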Similarly, in an Australian cohort (n=292), a scoliosis (Cobb angle >10°) was found in 41% of individuals with CP and was directly related to increasing GMFCS level. Severe scoliosis (Cobb angle >40°) was most common in children functioning at GMFCS IV and V (18% and 48%, respectively). Curves were also more common in young people with more severe limitations in fine motor function and the presence of dystonia or mixed movement disorders.^52^ There is limited research that has explored protective factors for preventing scoliosis in children with CP. In addition, the relationship between hip displacement and scoliosis and the inter-related musculoskeletal complications are not well established in child populations.^49^ In adult populations with CP, the association between asymmetrical limited hip flexion (<90°), pelvic obliquity and clinical assessment of scoliosis is well established.^53^ In children with CP, postural asymmetry may play a role in increasing the likelihood of developing scoliosis, windswept and contracted hips.^54^ While the convexity of scoliosis has been associated with the high side of pelvic obliquity in young people with CP,^55^ not all who have a scoliosis and pelvic obliquity will develop significant hip displacement, and the natural history and aetiological mechanisms which underpin severe scoliosis in young people with CP are not clear. These studies highlight associations between hip abnormalities and scoliosis in children and adults with CP, however a causative relationship remains unclear. There are few prospective studies in children with CP that have investigated the early biomarkers of progression and the inter-relationship between hip displacement and scoliosis, confirmed by radiology, within the same cohort. Also, while guidelines for hip surveillance have been available in Australia since 2008,^29^ there is currently no national clinical guideline for the routine identification and surveillance of scoliosis.

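### The 11-point detectable difference for scoliosis does not follow from 450 children and 25%: it is 13.2 points at 90% power, and wider if new onset is meant, because children who already have a curve are enrolled.

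*Protocol article*

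**What the plan says.** The section on sample size and power sets one analysable number: "The total number of participants with data in line with the primary study objectives is expected to be n=450". Attrition is already taken out: "This assumes 4 years of data from 90% of 500 enrolled participants". Power and significance level appear once, for hip displacement: "the AusCP MSK study will have 90% statistical power (α=0.05) to detect absolute differences between binary risk factor categories exceeding 12" per cent. The scoliosis sentence follows without restating either: "For scoliosis incidence, if an overall cumulative incidence of 25% is assumed, the study will be able to detect absolute between-group differences of >11" per cent. The paragraph closes by calling the power an underestimate because each child is measured every year.

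Three other places bear on the figure:

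- The primary objective (Aims and hypotheses) begins "Identify early biomarkers of onset/progression of musculoskeletal complications" and sets the scoliosis threshold at a Cobb angle above 10° at 8–13 years.
- Eligibility for Cohort A, in both the Australian and the New Zealand sample, requires CP, GMFCS III–V and age 4.00–9.99 years. It does not require the child to be free of a curve.
- The Introduction gives one rate at the 10° threshold, from an Australian cohort of 292: "a scoliosis (Cobb angle >10°) was found in 41% of individuals with CP and was directly related to increasing GMFCS level".

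**The concern.** Two things look wrong. First, the printed inputs do not appear to give 11 points at the only power level stated. Second, the hip sentence speaks of prevalence and the scoliosis sentence of incidence. Incidence in the sense of new curves can occur only in children without one at the start, yet the only denominator offered is all 450 and nothing in eligibility removes children who already have a curve.

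Scoliosis is one of the three complications in the primary objective, and onset is named there. If the study is believed to detect 11 points with 90% power when it does not, a null result for a scoliosis risk factor will be taken to exclude effects that it had a fair chance of missing.

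**Working it through.** **Inputs.** From the power section: N=450, overall rate p=0.25, α=0.05, and 90% power carried over from the hip sentence. Assumed, because not stated: a two-sided test and equal groups (225 each). A 4:1 split is mentioned only for hips ("Even when risk factors are unbalanced in a 4:1 ratio, we will be able to identify RRs of <0.74 or >1.35").

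**Formula.** For group rates p ± d/2 and n per group, the detectable difference d solves

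n·d² = [z(α/2)·√(2p(1−p)) + z(β)·√(2p(1−p) − d²/2)]²

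with z(α/2)=1.960, and z(β)=1.282 for 90% power or 0.842 for 80%.

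**Step 1: reproduce the plan's figure.** 2p(1−p)=0.375, so the first term is 1.960×0.6124=1.200.

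- 90% power, d=0.1317: second term 1.282×√(0.375−0.0087)=0.776. Sum 1.976, squared 3.904. Divided by d²=0.01734 this gives 225 per group. The detectable difference is **13.2 points** (31.6% against 18.4%). The arcsine and unpooled versions both give 13.1.
- 80% power: **11.4 points**.
- Power at d=0.11: (0.11×√225 − 1.200)/√(0.375−0.00605) = 0.450/0.607 = 0.740, so power is **77%**.
- Children needed for 11 points at 90%: (1.200+1.282×0.607)²/0.0121 ≈ 324 per group, **648** in all.

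**Step 2: look for a setting that gives 11.** At 90% power:

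| Setting | Detectable difference (points) |
|---|---|
| N=500, two-sided | 12.5 |
| N=450, one-sided | 11.9 |
| N=500, one-sided | 11.3 |
| N=450, two-sided, 25% as the reference group's rate, lower rate in the other group | 11.9 |
| Same, but one-sided | 10.9 |

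With 450 children, only the last reaches 11. It needs a one-sided test and treats 25% as one group's rate, whereas the article calls it the overall rate. The plainest match is 80% power. The hip difference shows the same pattern: 13.9 points at 90% and 12.1 at 80%, against 12 printed. The hip relative risk of 1.24 does not fit 80% power, however (12.1 points around 70% gives 1.19). The cause of the discrepancy therefore cannot be settled from the article.

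**Step 3: new onset only.** If 25% is the incidence among children without a curve at T1, N is 450×(1 − T1 prevalence). The article gives no T1 prevalence, so these values are assumptions:

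| Assumed T1 prevalence | At risk | 90% detectable difference (points) | Excess over 13.2 | Power at 11 points |
|---|---|---|---|---|
| 10% | 405 | 13.9 | 0.7 | 72.6% |
| 20% | 360 | 14.7 | 1.5 | 67.5% |
| 30% | 315 | 15.7 | 2.5 | 61.7% |

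At 80% power the same range is 12.0 to 13.6 points, so changing the stated power alone would not rescue 11 if onset is meant.

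**Step 4: two sensitivity scenarios.**

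- Overall rate 41% with N=450: 15.0 points at 90%; power at 11 points is 66%.
- 25% as the total by the last visit, with 5% or 10% already affected at T1. New cases are 450×0.20=90 among about 428 children, or 450×0.15≈68 among 405. The detectable difference is 12.7 or 11.9 points. That is narrower than 13.2 but still above 11, and the detectable relative risk rises from about 1.7 to about 1.9 or 2.1.

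**The case against.** The strongest reply is that 450 is a proper denominator. The outcome in the primary objective is curve status at an age, the planned mixed logistic models are not restricted to curve-free children, and retrospective spine X-rays are collected. Cumulative incidence can then mean ever having a Cobb angle above 10° by 8–13 years, and enrolling a child with a curve contradicts nothing. This stands. A reader might infer that the 450 and the 25% are incompatible on every reading, and the article does not support that. The at-risk problem arises only if new onset is meant, and the article does not say which it is.

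A reader might also infer that 41% shows 25% to be too low. It does not. The article gives neither the ages nor the GMFCS mix of that cohort. Its severe-curve rates (18% in GMFCS IV, 48% in V) lie between the Swedish rates at 10 years (5%, 20%) and at 20 years (35%, 75%), which suggests an older group than 8–13 years. The 25% is openly labelled an assumption, and a condensed article may leave its source to the full protocol.

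Nor does the article show how many children have a curve at T1. The Swedish age-10 rates (2%, 5% and 20% for GMFCS III, IV and V) are for curves above 40° and for an age at the upper limit of enrolment.

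Finally, the article says repeated measurements make its power an underestimate. A longitudinal model may gain something, but no correlation or gain is given, and cumulative incidence is one outcome per child. To restore 11 points at 90%, the repeats would have to be worth 648/450=1.44 times the children. The remark does not establish that.

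**Conclusion.** The concern holds in two parts of different weight.

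The firm part is arithmetic. The printed 11 points is not what 450 children and an overall rate of 25% give at 90% power: the figure is 13.2 points, and 11 points has 77% power. This assumes a two-sided test, equal groups and that the 90% applies to scoliosis as it does to hips. If 80% was intended, the figure is 11.4 and the power level needs to be stated.

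The conditional part is the denominator. If new onset is meant, the number at risk is below 450 by an amount the article does not give. At an onset rate of 25%, assumed T1 prevalences of 10–30% add 0.7 to 2.5 points to the 13.2. Most of the gap between 11 and the larger figures at low T1 prevalence is therefore the arithmetic, not the at-risk set. The 15.0 points at 41% is a sensitivity value and is not evidence against 25%.

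**What to change.** In the scoliosis sentence of the power section:

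- Say whether the endpoint is Cobb angle above 10° by 8–13 years or new onset in children without a curve at T1.
- For status in 450 children, replace the 11% with about 13 points at 90% power, or state 80% power and 11.4 points.
- For new onset, replace 450 by the expected number of curve-free children and recompute. The 13.9, 14.7 and 15.7 points above show the range for 10%, 20% and 30% with a curve at T1, and an expected prevalence should replace these assumed values.
- Optionally, give 15.0 points at 41% as a sensitivity figure.

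The cost is one reworded paragraph and a less favourable stated figure. No extra children, visits or data are needed.
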